*Daily Experience* We will use mobile-based ecological momentary assessment (EMA) to capture daily experiences. EMA is a brief survey designed to repeatedly assess individuals’ daily events, experience, and contexts multiple times a day to obtain “snapshots” of their everyday lives [46]. The EMA survey will be administered via a smartphone app, mEMA (illumivu). Illumivu is a commercially available EMA platform widely used by behavioral science researchers. EMA surveys will be prompted up to 6 times, at random intervals throughout the day, for 10 days. The random prompt window will be calculated by dividing the waking period (i.e., from participant’s typical wake time to typical bedtime) by 6, and one EMA survey will be prompted/delivered randomly during each time window. All EMA survey items to be used have been carefully selected from relevant previous studies. To capture *perceived racial discrimination and microaggression*, we will use adapted items from the Experiences of Discrimination (EOD) [47] and Gendered Racial Microaggressions Scale (GRMS) [48]. As in previous EMA studies [49], items for *mood/affective states* are chosen based on the two fundamental dimensions of affect suggested by the circumplex model (i.e., positive and negative affect). *Perceived stress* will be assessed using two items from the Perceived Stress Scale [50]. Each EMA survey will take no more than 3–5 min to complete. Responses to the EMA surveys will be automatically uploaded to the illumivu’s cloud-based server, and will be download for data analysis upon data collection completion.

*Salivary Cortisol* Saliva samples will be collected four times a day (i.e., at wakeup, 30 min after waking, before dinner, and right before bedtime) for 3 consecutive days (2 weekdays and 1 weekend days) to capture diurnal patterns of stress across the day. We will follow the collection procedures that have been used in previous studies that demonstrated high feasibility in women [51, 52]. We will use the Salivette device (Sarstedt, Inc.), a small, cotton dental sponge swab. Participants will be asked to place the swab in their mouth for 2 min and to store the samples in their home freezer as soon as possible after each collection. At the end of the 10-day study period, we will retrieve all saliva tubes from each participant and store them at a -80ºC freezer until they are assayed in batches.

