### Statistical considerations

Multilevel linear mixed-effect models will be used to account for repeated measures (for daily behaviors and daily experience) within an individual. We will separate the between-person and within-person effects by partitioning the variance. **Aim 1**: The daily experience predictors include (1) racial discrimination (i.e., daily EOD and GRMS score), (2) mood/affective states (i.e., daily average of positive and negative affect), (3) daily stress (i.e., daily average of perceived stress and diurnal cortisol rhythm such as total cortisol output, cortisol awakening response, diurnal cortisol slope). The daily behavior outcome variables include total daily moderate-to-vigorous physical activity minutes, total sedentary minutes, and sleep variables (i.e., SOL, WASO, TST). We will link the predictor and outcome at the day-level so that the acute impact of daily experience on behaviors can be examined. **Aim 2**: Outcome variables are indicators of cardiovascular health from lab-based measurements. We will first test the direct independent effects of daily behaviors on cardiovascular health outcomes using the mixed-effect models. Next, we will add the single-level and cross-level interaction terms to each multilevel mixed-effect model to test the moderation effects of daily experience. **Aim 3**: We will test the direct independent effects of neighborhood-level characteristics (predictors) on daily behaviors and daily experience (outcome variables) using the mixed-effect models. All tests of the hypotheses will be two-sided and an alpha level of 0.05. All analyses will be performed using SAS 9.4.

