*Sample size and power* Statistical power for evaluation of this study’s objectives was calculated using the macro by Westfall et al. that achieves power estimations based on linear mixed models [56]. Power calculations were computed based on a “fully-crossed” repeated measures design with a two-sided alpha of 0.05. This study will enroll 80 participants. Table 1 displays the statistical power based on possible effect sizes based on adjusted Cohen’s *d* values. Although pilot studies are commonly underpowered, adequate power will be achieved if our study effect is greater than *d* = 0.30. This estimate is indicative of a high likelihood of the planned sample size’s statistical power. We anticipate minimal missing data in the study. However, in the unlikely case of considerable missing data, we will conduct sensitivity analysis to account for different missing data mechanisms (missing at random or missing not at random), using appropriate approaches, such as multiple imputation, pattern-mixture, or selection models [57].

**Table 1 Tab1:** Effect sizes and statistical power yields for *n* = 80

Effect Size		Small			Moderate
Cohen’s *d**	0.10	0.20	0.30	0.40	0.50
Statistical Power (1-*b)*	0.17	0.51	0.84	0.98	0.99

*adjusted for repeated and correlated observations

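### Read as a wake-to-bed area, total cortisol output grows with hours awake, as sedentary minutes do, so Aim 1 can link the two without any stress effect

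*Protocol article*

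**What the plan says.** The protocol article, under Ambulatory assessments, has saliva collected "at wakeup, 30 min after waking, before dinner, and right before bedtime", and this "for 3 consecutive days (2 weekdays and 1 weekend days". Both ends of the sampling span therefore follow that day's wake time and bedtime.

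Under Statistical considerations, the Aim 1 stress predictors include the "diurnal cortisol rhythm such as total cortisol output, cortisol awakening response, diurnal cortisol slope". The outcomes are "total daily moderate-to-vigorous physical activity minutes, total sedentary minutes, and sleep variables (i.e., SOL, WASO, TST"; sedentary time is thus a raw total, not a share of waking time. Predictor and outcome are linked by day in mixed models that separate within- from between-person effects, and "All tests of the hypotheses will be two-sided and an alpha level of 0.05".

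The Introduction treats sleep, sedentary behaviour and activity as parts of one 24-hour day, and hypothesises that more stress goes with more sedentary time that day and worse sleep that night. The covariates under Other measures come from a one-time survey and are to be used as needed. Hours awake is not among them. The article gives no formula for total output.

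**The concern.** With these four samples, the natural computation of total output is the area under the cortisol curve from the first sample to the last. That area has more time to accumulate on a long waking day, and sedentary minutes accumulate over the same hours. Hours awake is then a common cause of predictor and outcome.

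The planned within/between split removes stable differences between women, but not something that differs from one day to the next within a woman. A person-level survey covariate cannot remove it either. The problem is shared exposure time, not the order of events, so it would remain even if every sample preceded the behaviour.

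The artefact points the same way as the hypothesis. A significant positive coefficient for this index could be read as support for an acute stress effect when it reflects only that longer days contain more of both quantities.

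**Working it through.** The article states no figure on this point. Its only computed figures, the power values in Table 1, do not enter the argument.

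**Inputs from the article.** 80 women; 3 cortisol days each, so 80 × 3 = 240 woman-days at most and 240 − 80 − 1 = 159 within-woman degrees of freedom; two-sided 5% test; sample times tied to waking and bedtime.

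**Inputs not in the article (assumed).** The cortisol profile, its day-to-day variation, the SDs of wake time and bedtime, and the sedentary share of waking time.

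**1. The coupling.** Take cortisol of 12 at waking, 17 at 30 min, then exponential decline of 0.115 per hour. The area to T hours after waking is 0.5 × (12 + 17)/2 + (17/0.115) × [1 − exp(−0.115 × (T − 0.5))].

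| Hours awake | Area | Area / hours |
|---|---|---|
| 15 | 127.2 | 8.48 |
| 16 | 130.2 | 8.14 |
| 17 | 132.9 | 7.82 |

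Each extra hour adds roughly 2% to the area and, at a 65% sedentary share, 0.65 × 60 = 39 sedentary minutes. The last column falls as the day lengthens, so dividing by hours awake replaces positive coupling with negative coupling.

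**2. Analytic size, middle setting.** Wake and bed SD 1 h each, independent; cortisol log-SD 0.35; sedentary share 62%; residual SD 75 min.
- SD of hours awake = √(1² + 1²) = 1.414 h.
- Sedentary minutes tied to hours: 0.62 × 60 × 1.414 = 52.6 min, so r(sedentary, hours) = 52.6/√(52.6² + 75²) = 0.574.
- Simulated r(cortisol area, hours) = 0.121.
- Induced r = 0.121 × 0.574 = 0.069.
- Expected test statistic ≈ 0.069 × √159 ≈ 0.88, so rejection ≈ P(Z > 1.96 − 0.88) + P(Z < −1.96 − 0.88) ≈ 14%. Simulation gave 15%.

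**3. Simulation, no true effect.** Profile as in step 1, day log-SD 0.2, sample log-SD 0.3, sedentary share 65%, residual SD 75 min, within-woman slope test. Ranges cover repeated runs.

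| Wake–bed correlation | SD 0.7 h | SD 1.0 h | SD 1.3 h |
|---|---|---|---|
| 0 | 8–9% | 18–19% | 34–37% |
| 0.3 | 7–8% | 10–12% | 21–23% |
| 0.6 | 6% | 6–8% | 11–12% |
| 0.8 | 5% | 5% | 7% |

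The correlation matters because Var(hours awake) = 2 × SD² × (1 − correlation). At SD 1 h, the SD of hours awake drops from 1.41 h at correlation 0 to 0.89 h at 0.6.

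**4. Wider grid, independent times, cortisol log-SD 0.2 to 0.5, residual SD 60 to 90 min.** Rejection is 5–8% at SD 0.5 h, 9–43% at 1 h and 18–89% at 1.5 h. If mainly wake time varies (1.2 and 0.3 h) it is 10–52%; if mainly bedtime varies (0.3 and 1.2 h), 5–16%, because evening cortisol is low and late hours add little area. Where inflation is material, nearly all false positives are in the hypothesised direction.

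**5. Total sleep time.** With independent times, rejection at SD 0.7/1.0/1.3 h is 7%/8%/13%. With correlation of 0.3 or more it is 4–7%.

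**6. Remedies.** Adding hours awake returns the sedentary test to 5.0% (log-SD 0.35) and 4.9% (log-SD 0.2). A fixed window after waking gives about 5%, at most 6%. Dividing by hours awake gives 18% and 41% in the same two settings, with negative induced r (−0.08 and −0.14).

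**The case against.** The index is not defined. The cortisol measures are introduced as examples, and the formula and day-level covariates may stand in a full protocol or SAP that is not shown. This is fair: the missing formula is not itself a fault, and the point is conditional on the wake-to-bed reading. What stands is that the sampling scheme, the raw-minute outcome and the same-day link together make that reading the likely one, and that reading needs correcting.

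The size is fragile. If a woman who rises later also goes to bed later, hours awake vary less and most of the inflation disappears. With correlation 0.6 and a larger day-to-day cortisol log-SD of 0.4, rejection at SD 0.7/1.0/1.3 h is 5%/6%/9%. This also stands.

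A reader might infer more than the documents support:
- *That Aim 1 is bound to find a cortisol–sedentary link.* In the middle setting 85% of such studies would find none.
- *That Aim 1 as a whole is compromised.* Discrimination, affect and perceived stress are not areas over the day, nor are the awakening response and the slope.
- *That mixing weekdays with a weekend day makes it worse.* The driver is hours awake. A weekend that shifts both times later may hardly change it, and the article gives no clock times.
- *That the sleep hypothesis is equally exposed.* The results for total sleep time show little effect.

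**Conclusion.** The point holds in a limited form. If total output is the area from the waking sample to the bedtime sample, it shares hours awake with total sedentary minutes. Neither the listed covariates nor the within/between split removes this, and the bias favours the hypothesis.

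Under the main assumed profile, with wake and bed SDs of 0.7 to 1.3 h, the false-positive rate of the nominal 5% within-woman test is about 6–35%: about 8–35% with independent wake and bed times, about 6–11% at correlation 0.6. Other plausible inputs take it from no inflation to severe inflation. Everything except the sample size, number of days, alpha and sampling times is assumed, so these figures show sensitivity and do not estimate the study's actual rate. The scope is one cortisol index, mainly against one outcome, on 3 of the 10 days. The correction is cheap enough to be worth making before analysis.

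**What to change.** Define total cortisol output over a fixed window after waking, for example 14 h, with the curve interpolated from the 30-minute, pre-dinner and bedtime samples.

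If the wake-to-bed area is kept, add that day's ActiGraph hours awake as a covariate in the models for sedentary minutes and MVPA minutes, both of which accumulate over waking time. Do not add it to the total sleep time models, because bedtime is part of the pathway to that night's sleep. Do not use area divided by hours awake as the remedy.

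The cost is a sentence or two of analysis text. ActiGraph sleep–wake data are already collected and enrolment was still open when the article was written. The fixed window also needs the time of each saliva sample, and it requires some interpolation, or extrapolation on short days, from few noisy samples. The hours-awake adjustment removes any stress effect that acts by lengthening the waking day, so its coefficient should be described as the association at a given number of hours awake.

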Overall, previous work has shown evidence of how neighborhood-level characteristics could impact individual behaviors and suggested a link between social stress and CVD risk. However, limited studies have focused on how an individual’s *actual experiences and behaviors in their everyday life* may contribute to validated, measurable, and quantifiable biomarkers of CVD risk. This knowledge gap is particularly critical for effective lifestyle intervention development, because in order to promote sustainable behavioral change, a lifestyle intervention will need to consider the everyday contexts of a person’s life in the real-world setting. Accordingly, this observational study aims to: (1) Examine the impact of daily experience (i.e., racial discrimination, affective states, stress) on health behaviors (i.e., physical activity, sedentary behavior, sleep) at the intrapersonal level among Black women. We hypothesize that there is an acute positive association between negative daily experiences and unhealthy behaviors, i.e., a higher level of stress will lead to more time spent in sedentary behaviors that day and poorer sleep at night. (2) Test the association between daily behaviors and impairments in biomarkers associated with vascular function/health (i.e., augmented systemic inflammation and oxidative stress, impaired peripheral/cerebral vascular function, increased large artery stiffness), as well as the impact of daily experience on the relationship between behaviors and vascular function. We hypothesize that unhealthy behaviors are positively associated with vascular function impairments, and daily experiences moderate this association, i.e., negative daily experiences will augment the negative impact of unhealthy behaviors on vascular function. (3) Explore the influence of neighborhood-level characteristics (i.e., social environment factors: i.e., neighborhood income and poverty, racial composition; and built environment context, such as park density and walkability) on daily experience and health behaviors. We hypothesize that unfavorable neighborhood characteristics are associated with unhealthy daily behaviors and negative daily experiences. Figure 1 outlines the study’s conceptual diagram.

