### Ambulatory assessments (procedures and measures)

*The 24-h Movement Behaviors* We will use the ActiGraph wGT3X-BT device to obtain measures of physical activity, sedentary behavior, and sleep. This device is a water-resistant, triaxial accelerometry that is used widely to capture continuous, high-resolution movement behaviors. Participants will wear the ActiGraph device on their non-dominant wrist at all times for 10 days. Collected data will be stored in the ActiGraph device’s internal memory and will be downloaded upon device returned at visit 2. We will apply the cut-points developed for wrist-worn ActiGraph accelerometer to define light-intensity activity, moderate-to-vigorous intensity activity, and sedentary behavior. We will follow the standard protocol to obtain sleep estimates from ActiGraph, which includes measures of sleep onset latency (SOL), time spent awake after sleep onset (WASO), and total sleep time (TST). In addition, we will use the daily electronic survey to capture self-reported sleep information to complement the ActiGraph-measured sleep data (e.g., to adjust sleep-awake time detected by ActiGraph as needed and obtain more information about perceived sleep quality). In the first daily electronic survey, adapted items from the Pittsburgh Sleep Diary will be included to capture self-reported sleep duration, sleep efficiency, and sleep quality [45].

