### Other measures

*Neighborhood environment (SDOH)* We will use the geographic information system tool, PolicyMap, to extract neighborhood-level built environment and social environment characteristics based on participants’ home addresses. We will extract neighborhood-level (e.g., at zip code-level or census track-level) social environment characteristics, including demographic indicators such as racial composition, diversity index (i.e., probability that two individuals chosen at random would be of different races/ethnicities), segregation (Theil index); neighborhood income and poverty, education attainment, employment and unemployment, and crime rate. We will also extract built environment characteristics such as park density, supermarket density, and fast-food restaurant density.

*Covariates* We will ask participants to complete a one-time online survey to assess their demographic information (e.g., age, education level, marital status, employment status, and household income), health literacy, past exposures to lifetime discrimination, and usual diet pattern. These variables will be used as covariates in our statistical models, as needed, and will be helpful in comparing our findings with previous studies and other larger population cohorts.

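### Aim 1 slopes of daily stress and affect on activity are open to confounding by the previous night's sleep, which the study records but names only as an outcome

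*Protocol article*

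**What the plan says.** All references are to the protocol article.

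- **Hypothesis (Introduction, aim 1).** It is directional and ordered in time: "a higher level of stress will lead to more time spent in sedentary behaviors that day and poorer sleep at night".
- **Model (Statistical considerations).** Mixed models with a within/between split: "We will separate the between-person and within-person effects by partitioning the variance". Predictor and outcome are then paired by day: "We will link the predictor and outcome at the day-level so that the acute impact of daily experience on behaviors can be examined".
- **Role of sleep in Aim 1 (same section).** The outcomes are "total daily moderate-to-vigorous physical activity minutes, total sedentary minutes, and sleep variables (i.e., SOL, WASO, TST"). Sleep is not listed among the Aim 1 predictors or as an adjustment variable.
- **Covariates (Other measures).** "We will ask participants to complete a one-time online survey to assess their demographic information", together with health literacy, lifetime discrimination and usual diet. Then: "These variables will be used as covariates in our statistical models, as needed".
- **Sleep data available (Ambulatory assessments).** The ActiGraph is worn day and night for 10 days. There is also a morning report: "In the first daily electronic survey, adapted items from the Pittsburgh Sleep Diary will be included to capture self-reported sleep duration".

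**The concern.** For any monitored day, the night before comes ahead of that day's stress and that day's activity. A poor night can plausibly raise stress and negative affect the next day. It can also change how the day is spent. The Introduction itself treats sleep, sedentary time and activity as parts of one 24-hour budget. If both paths exist, a day-level regression of sedentary minutes on stress picks up part of the effect of the night and presents it as an acute effect of the day's experience.

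Nothing named in the article blocks this. The within/between split removes stable differences between women, not differences between one woman's days. One-time survey variables have no within-woman variation, so as main effects they leave the within-woman slope unchanged.

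Aim 1 is meant to inform lifestyle interventions. A sleep effect read as a stress effect would point them at the wrong target.

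**Working it through.** **The plan's own figure.** No figure in the article bears directly on this point. Table 1 (power 0.84 at adjusted d = 0.30, n = 80) cannot be rebuilt, because the variance components behind the adjusted d are not given. It is internally consistent: a two-sided test with noncentrality 9.82 × d gives 0.166, 0.502, 0.838, 0.975 and 0.998, against the printed 0.17, 0.51, 0.84, 0.98 and 0.99. Nothing below depends on it.

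**Inputs from the article.** 80 women; 10 monitored days; two-sided alpha 0.05; cortisol on 3 days. Monitoring starts the day after Visit 1, so the first day may have no ActiGraph night before it. I use 9 days.

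**Assumed inputs.** Within a woman, all variables standardised: *a* is the effect of the previous night's sleep on stress or affect, and *b* its effect on the behaviour. The article gives neither. I take absolute values from 0.1 to 0.3. The true effect of stress is set to zero.

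**Step 1, spurious slope.** With stress = *a*·sleep + noise and behaviour = *b*·sleep + independent noise, the covariance of stress with behaviour is *ab*. Stress has unit variance, so the unadjusted slope is *ab*.

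**Step 2, standard error.** 80 × 9 − 80 person means = 640, so SE ≈ 1/√640 = 0.040. For three cortisol days, 80 × 3 − 80 = 160 and SE ≈ 1/√160 = 0.079.

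**Step 3, false-positive rate.** With λ = |*ab*|/SE, the rate is Φ(λ − 1.96) + Φ(−λ − 1.96). For *a* = *b* = 0.2 and 9 days, λ = 0.04/0.0395 = 1.01, giving Φ(−0.95) + Φ(−2.97) ≈ 0.17. The simulated columns use 2,000 data sets per setting and person-centred regression.

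| Absolute a, b | Spurious slope | 9 days, formula | 9 days, simulated | 9 days, simulated with previous night's sleep | 3 days, simulated |
|---|---|---|---|---|---|
| 0.1, 0.1 | 0.01 | 5.7% | 5.6% | 5.0% | about 5% |
| 0.2, 0.2 | 0.04 | 17.3% | 16.9% | 5.1% | about 8% |
| 0.3, 0.2 | 0.06 | 33.0% | 33.5% | 5.0% | about 12% |
| 0.3, 0.3 | 0.09 | 62.8% | 64.0% | 4.6% | about 19% |

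**Step 4, sleep as the outcome.** Here the previous night's value is the lagged outcome, and two forces oppose each other. Carry-over from night to night pulls the slope towards *a* × autocorrelation. Centring a short series on its own mean pushes the other way: with independent nights, centred neighbouring nights correlate at about −1/T, so *a* = −0.3 and T = 9 give −0.3 × (−1/9) = +0.033. Simulation at *a* = −0.3, with sleep coded so that higher is better, gives +0.034 at autocorrelation 0, about zero at 0.1, and −0.043 at 0.3. The sign changes within a plausible range. Adding the lagged value brought the false-positive rate back to about 5%.

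**The case against.** **Argument from silence.** The article gives three aims one short paragraph and does not say that the survey items are the only covariates. Time-varying terms are often left to a full protocol or analysis plan, and neither is shown. This has force: one can say that no such adjustment is named, not that none will be made. The point still stands, because the article does more than stay silent. It names a covariate source that cannot act within a woman, gives sleep the role of outcome, and calls the day-level slope an acute effect.

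Four stronger readings are tempting, and the documents do not support them.

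- **That Aim 1 is confounded.** Both paths are assumptions. At 0.1 and 0.1 the inflation is trivial. Open to confounding is as far as the text goes.
- **That the bias always favours the hypothesis.** It would for sedentary time if poor sleep raises both stress and sitting. For the three sleep outcomes the sign depends on an autocorrelation the article does not give (step 4).
- **That one size fits every predictor.** Cortisol has three days, with correspondingly smaller rates. For reported discrimination events, nothing in the article suggests that a bad night brings them about.
- **That adjustment also buys power.** The slope variance changes by (1 − ρ²)/(1 − a²), where ρ is the sleep-outcome correlation. With *a* = ρ = 0.3 the factor is 1, so 0.84 stays 0.84. With *a* = 0.3 and ρ = 0.2 the factor is 0.96/0.91 = 1.055. The noncentrality of 2.95 falls to 2.95/√1.055 = 2.88, and power to 0.82. The reason to adjust is bias, not precision.

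**Conclusion.** The point holds in limited form. As described, the Aim 1 slopes of momentary stress and affect on sedentary time and moderate-to-vigorous activity are open to confounding by a variable that precedes the exposure and is already collected. With 80 women, 9 usable days, no true effect and assumed standardised paths of 0.1 to 0.3, the false-positive rate lies between about 5-6% and just over 60%. With the previous night's sleep in the model it is about 5%. For the three cortisol days the range is about 5% to 20%. Where the study falls in these ranges cannot be read from the article. For sleep latency, wake after onset and total sleep time, neither the direction nor the size of any bias can be stated in advance. The change is worth making before Aim 1 is analysed; the design itself is sound on this point.

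**What to change.** In the Aim 1 models for moderate-to-vigorous activity and sedentary minutes, add the previous night's total sleep time and wake after sleep onset, person-mean centred, as within-woman covariates. Report adjusted and unadjusted slopes side by side. For the three sleep outcomes, add the previous night's value of the same variable as a sensitivity analysis.

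The cost is wording and model code; no new data are needed. Day 1 may lack a device-recorded night: either the diary entry stands in, or 9 of 10 days are used (720 of 800 woman-days). A lagged outcome in a short series carries some bias in its own coefficient, which is a further reason to keep it as a sensitivity analysis. Adjustment does not address same-day reverse causation, where activity changes stress, so the text should describe the slopes as same-day associations unless that is handled separately.

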### Lab-based assessments (procedures and measures)

The following assessments of cardiovascular health indicators will take place during participants’ in-person study visit.

A fasting venous blood sample will be taken for assessment of a comprehensive metabolic panel (e.g., glucose, glycated hemoglobin, blood lipid profile, etc.), as well as biomarkers associated with CVD risk [37], including markers of inflammation (e.g., CRP & vascular cellular adhesion molecule-1 [VCAM-1]), oxidative stress (e.g., thiobarbituric acid reactive substances [TBARS] & superoxide), and antioxidant status. Individual assays will be performed via enzyme-linked immunosorbent assay kits. Reactive oxygen species will be measured using electron paramagnetic resonance spectroscopy and superoxide fluorescence via peripheral blood mononuclear cells as previously described [38].

*Cerebral vascular function/health* will be measured utilizing trans-cranial Doppler ultrasound assessment of blood velocity in the middle cerebral artery (MCAv_mean_) and Doppler ultrasound measures of blood flow in the extracranial arteries (e.g., internal carotid artery [ICA]) during a hypercapnic challenge induced by breathing 6% Carbon dioxide. Cerebral function/health will be defined as the % increase and slope of the response in MCAv_mean_, ICA_flow_, and ICA or MCA conductance from baseline during hypercapnia. This methodological approach is routinely performed in our laboratory [39, 40]. Importantly, this is predictive of and a contributor to various neurocognitive conditions and cerebral vascular diseases [41, 42].

*Peripheral vascular function/health* will be determined by several commonly utilized approaches. Macrovascular function will be assessed as brachial artery vasodilation following a period of suprasystolic cuff occlusion (i.e., flow-mediated vasodilation). Microvascular function will be assessed as the % change in blood velocity from baseline following cuff release. Large elastic artery health will be assessed as carotid artery intima-media thickness as well as central and peripheral artery ß-stiffness, arterial compliance, and pulse wave velocity utilizing Doppler ultrasound (GE P5) and applanation tonometry (SphygmoCor® CPV Pulse Wave Velocity System). This is critical as impairments in these variables contribute to cerebral vascular dysfunction as well as other forms of CVD [43, 44].

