*Continuous Blood Pressure* To obtain additional insights regarding participants’ daily blood pressure pattern, we will use a wrist-worn continuous blood pressure device (Aktiia) to supplement our lab-based assessments. The Aktiia bracelet automatically tracks blood pressure throughout the day and has been clinically validated for accuracy [53, 54]. It is a wearable CE-marked Class IIa medical device that records optical signals at the wrist and transforms them into the blood pressure values using pulse wave analysis algorithms after an initial calibration procedure based on a series of oscillometric measurement performed by an upper arm cuff [55]. The Aktiia bracelet can provide up to 12 blood pressure readings each day. All data will be uploaded wirelessly through an Aktiia smartphone application to a research portal specific for this study.

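### Aim 2 plans multilevel models with cross-level terms for lab outcomes measured once per woman; only the between-woman part can be estimated, and it is a regression on 80 women

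*Protocol article*

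**What the plan says.** All references are to the protocol article.

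- **Outcome.** Statistical considerations, Aim 2: "Outcome variables are indicators of cardiovascular health from lab-based measurements". The lab section introduces these measures with "The following assessments of cardiovascular health indicators will take place during" the in-person visit. Study procedures places them at the first of two visits, and the Abstract calls the lab part cross-sectional. Monitoring starts the day after that visit. The return visit is described as handing back devices and saliva samples and completing an exit survey, with no repeat lab measurement.
- **Model.** The same section introduces mixed models because behaviours and experiences repeat within a woman, and says that between-person and within-person effects will be separated. For Aim 2 it states: "We will first test the direct independent effects of daily behaviors on cardiovascular health outcomes using the mixed-effect models". The next step is to "add the single-level and cross-level interaction terms to each multilevel mixed-effect model", as the test of moderation by daily experience.
- **Power.** "This study will enroll 80 participants". The calculation assumes a fully crossed "repeated measures design with a two-sided alpha of 0.05", and the text says "adequate power will be achieved if our study effect is greater than" d = 0.30. Table 1 gives power of 0.84 there.

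**The concern.** In Aims 1 and 3 the repeated variables are the outcomes, so a mixed model suits them. In Aim 2 they are the predictors and moderators, and the outcome does not repeat. A cross-level term needs a day-level component, and here the outcome has no day-level variance for that component to explain.

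Aim 2 carries the vascular hypothesis and the moderation hypothesis set out in the Introduction. If the stated model is fitted literally, a reader could take a structural zero for evidence of no within-person effect or no moderation. A between-person result could also be reported with far too small a standard error.

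**Working it through.** **Inputs.** 80 women, 10 days, two-sided alpha 0.05 and the Table 1 row are from the article. Intraclass correlations (ICCs) of behaviour, effect sizes and variance components are not given there; the values below are assumptions.

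**1. The plan's own power figure.** Table 1 gives 0.17, 0.51, 0.84, 0.98 and 0.99 for d = 0.10 to 0.50. A noncentrality of about 9.95d gives 0.166, 0.502, 0.839, 0.976 and 0.998. The fully crossed formula reaches this with assumed values (60 occasions, participant-by-condition variance 0.2, stimulus-by-condition variance 0, error 0.3): 1/(2√(0.2/80 + 0.3/(2·80·60))) = 9.94. The article gives no components, so the row is neither confirmed nor refuted. The point below does not depend on it.

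**2. Within-person and cross-level terms.** The within-person slope is Σ(x_it − x̄_i)(y_it − ȳ_i) / Σ(x_it − x̄_i)². With one outcome value per woman, y_it = ȳ_i on every day, so the numerator is 0 whatever the data. The same holds for day-level behaviour multiplied by person-level experience. In simulated fits (ICC 0.5, standardised effect 0.4) both terms were zero to the printed precision.

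**3. Likelihood.** For a random-intercept model on 80 × 10 rows, the log-likelihood contains −½·80·9·ln σ_e² = −360 ln σ_e². No within-woman sum of squares opposes it, so it grows without limit as σ_e² falls. At σ_e² = 10⁻⁸ this term alone is 360 × 18.42 = 6,631. In a simulated example the whole log-likelihood was:

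| σ_e² | 1 | 0.1 | 0.01 | 10⁻⁴ | 10⁻⁸ |
|---|---|---|---|---|---|
| log-likelihood | −862 | −33 | 796 | 2,454 | 5,770 |

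**4. Raw daily behaviour as predictor.** As the outcome ICC is pushed towards 1, the random-intercept slope goes from 0.050 (ICC 0.5) to 0.007 (0.9) and 0.00006 (0.999). Regression on person means averaged 0.508 in the same data.

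**5. Person-mean term included.** The between-person slope then equals ordinary regression on 80 means (0.4070 against 0.4070 in one fit). Its standard error does not: 0.027 against 0.086, a ratio of 3.2. The cause can be shown. Software that profiles out the residual variance sets the between-woman variance to about RSS/(800 − 3), where the regression on means uses RSS/(80 − 2). The ratio of standard errors is √(797/78) = 3.20. A test with a standard error 3.2 times too small rejects a true null with probability 2[1 − Φ(1.96/3.2)], about 54%. A small null simulation (ICC 0.4) rejected in 88 of 150 runs, against 12 of 150 for regression on means. These fits used one Python package; the article names SAS 9.4, which was not run.

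**6. If the random intercept were dropped (not planned).** Pooling 800 rows understates the slope variance by about 1 + 9·ICC, so false-positive rates are about 2[1 − Φ(1.96/√(1 + 9·ICC))]:

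| Behaviour ICC | 1 + 9·ICC | Formula | Simulated (two runs) |
|---|---|---|---|
| 0.2 | 2.8 | 24% | 25%, 28% |
| 0.4 | 4.6 | 36% | 36%, 36% |
| 0.6 | 6.4 | 44% | 43%, 44% |

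Regression on person means held about 5%.

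**7. Power with one row per woman.** Converting by r = d/√(d² + 4), an assumption, power is Φ(√77·atanh r − 1.96). At d = 0.30, r = 0.148 and √77·atanh r = 1.31, giving 0.26. The row for d = 0.10 to 0.50 is 0.07, 0.14, 0.26, 0.41 and 0.58. If 0.30 is instead read directly as a correlation, power is 0.78. About 80% power needs a correlation of about 0.31.

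**The case against.** The strongest reply is that the article promises to separate between-person from within-person effects. A person-mean term recovers the between-person association, which is the kind of association the Introduction hypothesises. This stands. A reader might infer that Aim 2 cannot estimate behaviour effects at all, or that the moderation hypothesis is untestable; the documents do not support either. The Introduction does not tie moderation to a level, and single-level terms are planned beside the cross-level ones. A product of person means tests the hypothesis. What does not survive is the within-person half, the cross-level terms, and trust in the standard error from copied rows.

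Second, day-level linkage is written only under Aim 1, copying the outcome across days is stated nowhere, and a condensed article leaves detail to an analysis plan. That is fair as to layout. But cross-level terms in each multilevel model are stated text, and no layout makes them estimable for an outcome measured once.

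Third, the 24% to 44% false-positive rates belong to a model without a random intercept, which the article does not propose. They show the cost of one tempting workaround and are not the plan's error rate.

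Finally, a reader might infer that wristband blood pressure, which does repeat, ought to be an Aim 2 outcome. The article includes it "to supplement our lab-based assessments". Leaving it out of Aim 2 is a choice of scope and not an error.

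**Conclusion.** The point holds as a wrongly stated model, not as a flaw in the data. For lab outcomes measured once per woman, within-person behaviour effects and cross-level interactions are structurally zero, and the likelihood is degenerate. These results follow from the design and need no assumed value. The between-person effect is estimable and equals a regression on 80 means. Its standard error from replicated rows is unreliable: about 3.2 times too small in the package used, and unverified in SAS.

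Table 1 is not shown to be wrong; it describes a repeated-measures design that Aim 2 does not have. With one row per woman, power at a nominal 0.30 is 0.26 or 0.78, depending on how the effect size is read, against 0.84 in the table. Table 1's effect size is already adjusted for repeated observations, so this comparison is indicative only.

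**What to change.** For all lab outcomes in Aim 2:

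- State a linear regression with one row per woman (n = 80) of the outcome on her mean behaviour. A multilevel latent-variable model for a person-level outcome is an alternative. It would also allow for the unreliability of a 10-day mean: reliability 10·ICC/(1 + 9·ICC) is 0.71, 0.87 and 0.94 for ICCs of 0.2, 0.4 and 0.6.
- Test moderation by the person-level product of mean behaviour and mean experience.
- Delete the within-person and cross-level terms for these outcomes. Aims 1 and 3 are unaffected.
- State that Table 1 does not apply to Aim 2, and give the precision or detectable correlation for 80 women.

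The cost is wording only; no new data or visits are needed. The downside is that the stated precision for Aim 2 will look less favourable.
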